## Background

Eighty percent of older adults have at least one chronic disease and 65% have at least two [1, 2], leading to an increased risk of polypharmacy [3]. Sensory functions, movement and cognitive capacity impair with aging, thus increasing immobility, frailty, dependence, health-care utilisation, risk of falling and fear of falling [3–6]. The incidence rate of falls of people aged 65–90 is 0.3–0.4 and that of ‘recurrent falls’ is 0.1 per person and year [7], and 21–85% of older adults are afraid of falling [8]. About 10–20% of falls lead to injuries, 5% to fractures and 1–2% to femoral neck fractures [5]. After femoral neck fractures, only 33–40% of patients regain their previous basic everyday competences (e.g., eating and body care), only 14–21% resume their competence for instrumental activities (e.g. shopping and phone calls) and 30% die within 1 year [5, 9]. After falls and hip fracture, 30–50% of people express their fear of falling, which reduces physical activity, mobility and self-confidence. The rates of falls, social isolation, institutionalisation and mortality have increased [5, 9]. The risk factors for falls in the elderly include the following: history of a fall, lower-extremity weakness, impairment of cognitive and sensory functions (e.g. proprioceptive sensitivity, vestibular system, vision and hearing), chronic disease (e.g. cerebrovascular or cardiovascular, Parkinson’s disease, osteoarthritis of the knee and diabetes), drugs particularly those affecting the central nervous system, type of footwear and safety hazards in the home environment [10, 11].

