### Key eligibility criteria

Included will be adults who are at least 65 years, have a chronic disease (e.g. musculoskeletal, neurological or cardiovascular), have an increased risk of falling [Berg Balance Scale (BBS) score 49 or less and a self-reported history of imbalance], are able to participate in 1 h group-based sessions and are able to leave home on their own. There is no restriction with respect to their domicile.

Excluded will be patients with medical conditions limiting participation (e.g., terminal illness, heart failure NYHA III-IV, unstable angina pectoris, uncontrolled seizure disorder, decompensated lung disease, cancer in the advanced stage, chemo- or radiotherapy ongoing or during the last 3 months or amputation of one or both legs); complete dependence on a rollator (wheeled walker); major visual, hearing or language problems affecting the understanding of trial documents and procedures; major cognitive impairment (MoCA score 18 or less); conditions affecting the participation of group classes (e.g. high risk for individual support, urge incontinence, personality disorder and substance use disorders); life expectancy less than 1 year; permanent confinement to bed to be expected in less than a year; participation in regular Tai Chi or EYT exercises within the last 6 months and participation in vigorous sports for exercise within the last month.

A specific recruiting strategy will strengthen the enrolment of elderly people who are economically disadvantaged and living a reclusive life.

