### Outcomes

*Primary outcome* Risk of falling is the incidence of experiencing at least one fall within 6 months. A fall is defined as ‘an unexpected event in which the participants come to rest on the ground, floor or lower level’ [42]. The frequency of falls is self-reported daily in the fall diaries and ascertained during the monthly phone calls. Its assessments follow international guidelines [42].

*Secondary outcomes* are the risk of falling at month 12; the number of falls and injurious falls categorised into ‘moderate’ (sprains, bruises, scrapes, joint injuries and needing medical care) and ‘serious’ (fracture, head injury, tendon rupture, inpatient care and requiring stitches) [43]; balance and mobility (BBS [44]); cognition (MoCA [45]); fear of falling (short FES-I [46]); mood (GDS-15 [47]); health status (SF-12 [48]); instrumental activities of daily living (IADL [49]); use of medical and non-medical services (FIMA [50]); medications (total number and classes of fall-risk-increasing drugs [51]); adherence to practicing in groups and at home (participants’ lists and training diary); inner correspondence/peaceful harmony with practices (ICPH [52]), use of standard fall prevention measures and subjective estimation of motivational support; and contamination with Tai Chi or EYT in the non-Tai Chi and non-EYT groups (self-designed questionnaires, see Supplementary file 1, 2, 3 and 4)).

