### Participant timeline

The time schedule of enrolment, interventions, assessments and visits for participants is shown in Table 1.

**Table 1 Tab1:** Participant timeline of the visits and assessments

VISITS	Pre-Treatment (Screening, Waiting time, Baseline/Visit 1 Randomisation)				Treatment					Post-Treatment Follow-up	
						Phone Visit 2–3	Visit 4	Phone Visit 5–6	Visit 7	Phone Visit 8–12	Last Visit, EOT
**TIME**			**Week − 4 to Day − 1**		**Day 0**	**Month 1 & 2**	**Month 3**	**Month 4 & 5**	**Month 6**	**Month 7–11**	**Month 12**
**Pre-Screening**	**X**										
**Waiting time**		**X**									
**Randomisation**				**X**							
**Informed consent**			**X**								
**In-, exclusion criteria**			**X**								
**Demographic Data**			**X**								
**Handing out Study Book**					**X**						
**Fall prevention information**					**X**						
**Recommendation to visit primary care doctor**					**X**						
**Start treatment or control per participant**					**X**						
**Review fall diary**						**X**	**X**	**X**	**X**	**X**	**X**
**BBS**			**X**				**X**		**X**		**X**
**MoCA**			**X**				**X**		**X**		**X**
**IADL**			**X**				**X**		**X**		**X**
**Medications**			**X**				**X**		**X**		**X**
**Baseline Questions**			**X**								
**Short FES-I**			**X**				**X**		**X**		**X**
**GDS-15**			**X**				**X**		**X**		**X**
**SF-12**			**X**				**X**		**X**		**X**
**ICPH (only EYT and Tai Chi group)**							**X**		**X**		
**FIMA**			**X**				**X**		**X**		**X**
**Safety; complications**						**X**	**X**	**X**	**X**	**X**	**X**
**Adherence, motivation, additional interventions**									**X**		

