### Statistical analysis

The primary efficacy analysis will be performed according to the intention-to-treat principle. All randomised participants will be analysed as belonging to their randomised arm, regardless of whether they refused therapy or whether other protocol deviations are known.

For the analysis of the primary endpoint fall (yes, no) within 6 months, a time-to-event methodology will be applied using the time to the first fall to account for the potentially incomplete observation times of the participants. This is considered to be more efficient than an analysis of the binary endpoint fall (yes, no), therefore leading to a gain in power. For participants who do not fall within the six-month observation period, the time to last contact will be used as censored observation. Death without a previous fall will be regarded as a competing event in the analysis. A Cox regression model will be used to test the efficacy of EYT versus Tai Chi versus standard care in reducing the risk of falling within 6 months after handing out the study book. The model will include the intervention type, trial site, BBS score and age as the independent variables. To account for multiplicity issues in this three-group comparison, a closed test procedure at the two-sided level alpha of 5% will be used. That is, the global null hypothesis of no differences between any of the three intervention types will be tested first, and if it can be rejected, pairwise group comparisons will be conducted each at the two-sided level alpha of 5%. Hazard ratios between the interventions will be calculated from the model with a two-sided 95% CI. In addition to the overall comparison of the treatment arms, a comparison of treatments in the key participant subgroups will be of interest. The treatment effect will be estimated separately in the participants defined by different diagnoses (present vs. absent) from the regression models, including the interaction between treatment and diagnosis.

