For the analysis of the secondary endpoint total number of falls per participant within 6 months after handing out the study book, a negative binomial regression model will be used to test the efficacy of EYT versus Tai Chi versus standard care. A negative binomial is preferred over a Poisson regression because of the potential overdispersion. Fall rates for participants with follow-up times of less than 6 months will be adjusted by accounting for their exposure time. The model will include intervention type, trial site, BBS score and age as the independent variables. The incidence rate ratios between interventions will be calculated from the model with a two-sided 95% CI. To consider the potentially present excess of zeroes, a zero-inflated negative binomial model will be used as a sensitivity analysis. Other secondary endpoints will be analysed with the appropriate regression models.

Safety analyses will be performed for all participants for whom one of the interventions is started, and participants will be analysed according to the intervention received. The rates of adverse events and serious adverse events will be calculated with a two-sided 95% CI. No formal interim analyses of the efficacy endpoints will be performed.

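### Both fall models could adjust for cognition and fall-risk drugs, which are recorded before treatment; leaving them out is valid but forgoes some efficiency

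*Protocol article*

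**What the plan says.** The Statistical analysis section of the protocol article fixes the covariates twice. For the primary Cox model: "The model will include the intervention type, trial site, BBS score and age as the independent variables". For the negative binomial model of the number of falls: "The model will include intervention type, trial site, BBS score and age as the independent variables".

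The Background gives the protocol's own list of predictors: "The risk factors for falls in the elderly include the following: history of a fall, lower-extremity weakness, impairment of cognitive and sensory functions". It goes on to chronic disease, "drugs particularly those affecting the central nervous system", footwear and hazards at home.

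Table 1 (Participant timeline) marks MoCA, Medications, IADL, short FES-I, GDS-15, SF-12, FIMA and an unspecified row called "Baseline Questions" in the screening and baseline column. MoCA also serves eligibility, through the exclusion for "major cognitive impairment (MoCA score 18 or less". The Outcomes section shows what is taken from the drug record: "medications (total number and classes of fall-risk-increasing drugs". The entry criterion nearest to fall history is "a self-reported history of imbalance", which every participant must have.

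Diagnoses enter only through subgroup interactions. Randomisation is stratified by site, and site is in both models.

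**The concern.** Cognition and drugs are named as predictors of the endpoint and measured before treatment, yet not used. In a Cox model, omitting a prognostic factor moves the hazard ratio towards 1. In a negative binomial model, it adds to the dispersion and so to the standard error. Either way some power is left unused, although the data are already in hand.

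The protocol's own reasoning points towards adjustment. It chooses a time-to-event analysis partly for its gain in power, and it adjusts the cost model for baseline costs.

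Timing matters because the Blinding section says that the statistical analysis will not be blinded and relies on confirmatory analyses being prespecified in the protocol. Covariates added after outcomes by arm have been seen would carry little weight.

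**Working it through.** **1. The plan's own sample size.** Inputs from the Sample size section: 50%, 35%, 35%; two-sided 5%; 80% power; 155 per group; 550 randomised.

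The mean proportion is 0.40. The effect size is (0.10² + 0.05² + 0.05²)/(0.40 × 0.60) = 0.015/0.24 = 0.0625. A chi-square test on 2 df needs noncentrality 9.635 for 80% power, so n = 9.635/0.0625 = 154.2, that is 155 per group, with power 80.2%. The plan's figure reproduces, and it takes no credit for any covariate.

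**2. The pairwise figure.** The two-proportion formula is Φ{(|p₁−p₂|√n − 1.96√(2p̄q̄))/√(p₁q₁+p₂q₂)}. For 50% vs 34.3% with n = 155 it gives 80.2%, as stated. For 50% vs 35%, the effect planned for, it gives 76%. In a time-to-event analysis the hazard ratio is ln 0.65/ln 0.50 = 0.62 with 155 × 0.85 = 132 events. Schoenfeld's formula then gives Φ(√(132/4) × |ln 0.62| − 1.96), about 78%.

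**3. What one extra covariate adds to the Cox model.** This was simulated with 2,000 trials per setting, 155 per group, calibrated so that the marginal six-month risks stay at 50/35/35%. One covariate Z is already adjusted for (log hazard ratio 0 or 0.3 per SD, standing in for BBS or age). One further binary predictor X with 50% prevalence is omitted or added. The strengths of Z and X and the prevalence of X are assumptions. With no extra predictor (X hazard ratio 1), global power is 82 to 83%.

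| Hazard ratio of X | Global test, X omitted → added (Z = 0) | Same (Z = 0.3) | Global and EYT vs standard care both significant (Z = 0) | Same (Z = 0.3) |
|---|---|---|---|---|
| 1.5 | 81.6 → 82.2% | 83.5 → 83.9% | 72.0 → 73.2% | 75.7 → 75.7% |
| 2.0 | 81.5 → 84.0% | 84.2 → 86.0% | 72.9 → 75.4% | 76.3 → 78.2% |
| 2.5 | 82.5 → 85.8% | 83.8 → 88.1% | 73.9 → 77.7% | 76.3 → 81.0% |
| 3.0 | 82.2 → 87.4% | 84.8 → 90.2% | 73.8 → 79.0% | 77.0 → 82.9% |

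The Monte Carlo standard error of a single power is a little under 1 point. Each pair uses the same simulated trials, so the differences are more precise. At 183 per group (Z = 0.3), global power goes from 89.9 to 91.1% for hazard ratio 2 and from 89.4 to 93.5% for hazard ratio 3. The estimated hazard ratio moves from 0.61 to 0.58 when a predictor of hazard ratio 3 is added.

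**4. The negative binomial model.** Assumed: rate ratio 0.65, control mean μ of 0.8 to 1.2 falls, dispersion k of 0.5 to 1.5, X with 50% prevalence, 155 per arm. The variance of the log rate ratio is the sum over the two arms of (1/μ + k)/155. Adjusting for X lowers k according to (1 + k) = (1 + k_adj)(1 + c), where c is the squared coefficient of variation due to X.

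Example with X rate ratio 3, k = 1, μ = 1.2: c = 5/4 − 1 = 0.25 and k_adj = 2/1.25 − 1 = 0.60. The variance falls from (0.833 + 1.282 + 2 × 1.0)/155 = 0.0266 to (0.833 + 1.282 + 2 × 0.6)/155 = 0.0214, and power rises from 75.3 to 83.8%.

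Over the whole grid the gain is 1 to 2 points (rate ratio 1.5), 3 to 4 (2.0), 5 to 7 (2.5) and 6 to 9 (3.0). This formula puts every participant at the arm mean, which flatters the adjusted model. Computing the variance within each level of X, with X-specific means and k_adj, and pooling by inverse variance lowers the example to 81.5%. The range across the grid is then about 1 to 6 points instead of 1 to 9.

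**5. Room in the model.** Expected first falls are 155 × (0.50 + 0.35 + 0.35) = 186, or 183 × 1.20 = 220 with everyone randomised. Two or three more terms are easily carried.

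**The case against.** The case for leaving the models alone is good. Site, BBS and age form a short, prespecified set that includes the stratification factor. The test keeps its error rate, and how many covariates to add is partly a matter of taste. All of that stands.

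Three stronger readings are tempting and should be set aside:

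- **That the trial is underpowered because of the covariate list.** The 80% was claimed for an unadjusted global test; it reproduces, and the Cox model meets it without further terms. Pairwise power at 35% is below 80%, but the plan does not claim otherwise: it states 80% for EYT against standard care at 34.3%.
- **That the protocol collects fall history and ignores it.** Fall history comes first in the Background list, but the article does not show that it is recorded. The content of the Baseline Questions is not given, and the full protocol is not at hand. Short FES-I is recorded, but fear of falling is not in that list of risk factors. Only cognition and drugs are clearly both listed and measured.
- **That chance imbalance would bias the comparison.** Allocation is concealed and the test already allows for chance imbalance. Open-label conduct does not create it.

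Some other limits also stand. Everyone enters with BBS of 49 or less and a history of imbalance, and MoCA scores of 18 or less are excluded, so further predictors may be weaker than assumed. Part of the shift in the Cox hazard ratio reflects that adjusted and less adjusted hazard ratios are different quantities. Missing baseline values would need handling.

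**Conclusion.** The point holds as a cheap improvement, not as an error. Both fall models leave out cognition and drugs, which the protocol names as risk factors and records before treatment. For one added predictor, the gain in global Cox power is under 1 point at hazard ratio 1.5, about 2 to 2.5 points at 2.0 and about 5 points at 3.0. The gain in power for both the global test and EYT against standard care to succeed is of similar size. For the pairwise negative binomial test it is 1 to 9 points by the simple formula, with the upper end nearer 6 on the finer calculation.

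The direction is secure. The size rests wholly on assumed strengths beyond BBS, age and site, an assumed 50% prevalence and, for the count model, assumed fall rates and dispersion. If the added covariates are weak, the gain is negligible.

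**What to change.** Before any outcome data by arm are seen, amend the protocol or fix in the analysis plan that both models also contain the baseline number of fall-risk-increasing drugs and baseline MoCA. Short FES-I is optional. If the Baseline Questions record falls in the previous 12 months, add that too. State the form of each term, and give a simple rule for missing baseline values so that all randomised participants stay in the intention-to-treat analysis. Keep the model with site, BBS and age as a prespecified sensitivity analysis, and say that the reported hazard ratio is conditional on the listed covariates.

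The cost is a few lines of wording, a few model terms against about 186 to 220 expected events, and handling of occasional missing values. No new data are needed for the drug and MoCA terms.

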### Interventions

Participants will be randomly allocated to receive standard care plus EYT or plus Tai Chi or standard care only (control).^1^

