#### When

Group sessions will take place twice a week during weeks 1–12 and once per week during weeks 13–24. The intensity is higher in the first weeks, taking into account the learning curve, and is reduced later when individual practicing has become routine. The participants are instructed to practice exercises at home for a minimum of 20 min during three non-class days.

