### Complications

The complications that can arise from EYT, Tai Chi or other exercises will be collected monthly. A complication is any untoward medical occurrence such as any unfavourable and unintended sign, symptom, or disease that is possibly related to the study intervention. Not regarded as complications are conditions that were already present at the time of the informed consent or aching muscle, which is to be expected. Starting with the open questions, participants are asked about any untoward medical occurrences or unplanned medical visits. In case of a possible relation to the intervention, these occurrences are documented, including severity and outcome. Moreover, therapists or teachers can inform the trial sites about the complications. Falls and injurious falls are documented as primary outcomes, and injuries are reported as complications in case they occurred during training. Further information on safety will be derived from the FIMA, which assesses healthcare utilisation such as physician contacts and hospitalisations.

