### Retention

Participants will be compensated for their travel costs: €110 for the first 6 months and €20 each for the screening and follow-up. If necessary (e.g. social welfare)*,* up to 15% of participants can receive further reimbursement of public transportation costs to visit group classes. Compliance with the trial procedures will be supported through appreciation, expressed gratefulness, giving participants sufficient time to be heard and seen, detailed explanation of the purpose and necessity of such studies to improve elderly care and a small token during every visit of the trial site (e.g. a post card with motifs from art, nature or aphorisms).

Participants may withdraw from the group classes or from the study for any reason at any time. The investigator may withdraw a participant from the intervention if the risks outweigh the benefit or if the inclusion/exclusion criteria are severely violated. Nevertheless, further follow-up visits and the assessment of the trial endpoints will be attempted to conduct an analysis according to the intention-to-treat principle.

Following the recommendation of public and patient representatives (PPR), EYT therapists, Tai Chi teachers and study personnel will receive a 3 h personal and written refresher training in appreciating, encouraging, non-judgmental communication and managing challenges of the group situation provided by a communication trainer. The EYT therapists and Tai Chi teachers will also receive a motivation concept on elderly people to comply with regular exercises, with a specific focus on the elderly living a reclusive life. The motivation concept is based on published research [21, 56, 57–61] and expert consultation.

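### Grouping safety data by intervention received breaks the randomised comparison, because standard care is part of every arm

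*Protocol article*

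**What the plan says.** In the protocol article, Statistical analysis defines the safety set and its grouping in one sentence: "Safety analyses will be performed for all participants for whom one of the interventions is started, and participants will be analysed according to the intervention" that they received. Rates of adverse and serious adverse events with 95% confidence intervals follow. No adverse event table by randomised arm is stated.

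Interventions describes an add-on design: "Participants will be randomly allocated to receive standard care plus EYT or plus Tai Chi or standard care only (control"). Under What, standard care consists of a fall-prevention brochure and a recommendation to see the primary care physician. Table 1 places both on Day 0 for participants generally, next to the row "Start treatment or control per participant". The ICPH row, by contrast, is marked as applying to the exercise groups alone. The section on blinding counts standard care as one of the three trial interventions.

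For efficacy, Statistical analysis keeps every participant in the randomised arm, including those who refuse therapy. Retention adds: "Participants may withdraw from the group classes or from the study for any reason at any time". Home practice belongs to both exercise programmes (When): "The participants are instructed to practice exercises at home for a minimum of 20 min during three non-class days". The Complications section defines a complication as an untoward medical occurrence such as "any unfavourable and unintended sign, symptom, or disease that is possibly related to the study intervention", and takes further safety information from FIMA, including hospitalisations.

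**The concern.** As-received grouping works when each arm gets something different. Here the comparator is contained in the other two arms. Everyone starts standard care on Day 0, so the condition that an intervention was started excludes practically nobody. A participant in an exercise arm who takes up no EYT or Tai Chi has received what the control arm received, and the stated rule then places that person in the standard care column. The article expects such people, since its efficacy rule mentions refusal of therapy.

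The reverse move is also open. Contamination with Tai Chi or EYT is a listed outcome, so a control participant who takes either up could be reclassified.

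The safety columns would then differ from the randomised arms by a selection made after randomisation, and one person could count as Tai Chi for benefit and as standard care for harm. What is at stake is whether a difference in adverse event rates can be attributed to the interventions.

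**Working it through.** **Plan's own figure.** The article gives no safety rate and no share of non-starters, so there is nothing to reproduce. The nearest number is the allowance in Sample size: 3 × 155 = 465 needed, 550 randomised, 85/550 = 15.5%. It covers non-compliance and incomplete observation together and is not an estimate of non-starters.

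**Step 1: where each participant goes**

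| Participant | Efficacy group | Safety group, read literally |
|---|---|---|
| Exercise arm, attends a class or practises at home | randomised arm | EYT or Tai Chi |
| Exercise arm, does neither | randomised arm | standard care |
| Control, no EYT or Tai Chi | standard care | standard care |
| Control, takes up EYT or Tai Chi | standard care | could become EYT or Tai Chi |

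**Step 2: inputs and formulas.** Assumed: q = share of non-starters in each exercise arm, a = risk in starters, v = risk in non-starters, c = risk in the control arm. Take 183 per arm (550/3) and ignore contamination.

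- By randomised arm: exercise (1 − q)a + qv; standard care c.
- As received: exercise a; standard care (c + 2qv)/(1 + 2q).
- Group sizes as received: 183(1 − q) in each exercise group and 183(1 + 2q) in standard care. At q = 10% this is about 165, 165 and 220.

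**Step 3: all-cause events, no true effect.** With no effect, c = (1 − q)a + qv, so all three randomised arms have the same risk. The as-received difference then reduces to 3q(a − v)/(1 + 2q), and its sign is that of a − v. With a = 8%:

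| q | v | Every randomised arm | Standard care as received | Exercise as received | Ratio |
|---|---|---|---|---|---|
| 5% | 20% | 1.0 + 7.6 = 8.6% | (8.6 + 2.0)/1.1 = 9.6% | 8.0% | 0.83 |
| 10% | 30% | 3.0 + 7.2 = 10.2% | (10.2 + 6.0)/1.2 = 13.5% | 8.0% | 0.59 |
| 15% | 30% | 4.5 + 6.8 = 11.3% | (11.3 + 9.0)/1.3 = 15.6% | 8.0% | 0.51 |
| 10% | 8% | 0.8 + 7.2 = 8.0% | (8.0 + 1.6)/1.2 = 8.0% | 8.0% | 1.00 |
| 10% | 4% | 0.4 + 7.2 = 7.6% | (7.6 + 0.8)/1.2 = 7.0% | 8.0% | 1.14 |

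The true ratio is 1 in every row. Higher-risk non-starters make exercise look safer, equal risk changes nothing, and lower-risk non-starters make exercise look less safe.

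**Step 4: exercise-related complications.** Take a = 10% and no such events in non-starters or controls. By randomised arm the exercise rate is (1 − q) × 10%, which is 9.5%, 9.0% and 8.0% at q = 5%, 10% and 20%. As received it is 10.0% throughout. The difference from standard care rises by 0.5, 1.0 and 2.0 points, against exercise. With a background rate of 2% in controls and non-starters and q = 10%, the difference goes from 9.2 − 2.0 = 7.2 points to 10.0 − 2.0 = 8.0 points.

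**The case against.** As-received safety grouping is conventional, and the article nowhere says that exercise-arm non-starters count as standard care. The full protocol or a statistical analysis plan may define what counts as received. Because home practice is part of both programmes, someone who misses every class may still have received the intervention. Entrants must be able to attend one-hour sessions, and classes begin straight after allocation, so non-starters may be few. These points stand: the group at issue is limited to people with no class and no home practice, and its size is unknown. They do not change what the published sentence does when applied as written to an add-on design.

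A reader might infer that the rule hides harm by making EYT and Tai Chi look safer. The article does not support that as a general statement. The events it documents as complications are those possibly related to the intervention, and for these the shift goes against exercise. The favourable shift needs all-cause events and non-starters at higher risk. Its likeliest source is FIMA, yet FIMA and injurious falls are listed secondary outcomes, and nothing clearly puts them under the safety grouping. Nor is it right that every harm-related measure is grouped as received, because the primary falls analysis is by randomised arm.

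**Conclusion.** The point holds in limited form. The stated rule, read literally, moves unexposed exercise-arm participants into standard care and could move contaminated controls out of it, so the adverse event and serious adverse event comparison is no longer randomised. The direction depends on the event type. All-cause events favour exercise only if non-starters are at higher risk, whereas exercise-related complication rates in the exercise arms rise.

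The size cannot be derived from the article. The spurious ratios of 0.83 to 0.51, and the shifts of 0.5 to 2.0 points the other way, rest wholly on assumed non-starter shares (5–15% and 5–20% respectively) and assumed event risks. They show what the rule can do and do not forecast this trial. The primary efficacy analysis is unaffected.

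**What to change.** - Present adverse event and serious adverse event rates by randomised arm for every between-arm comparison. Do the same for FIMA hospitalisations wherever they serve as safety information.
- Keep an exposure-based table of complications for participants who started EYT or Tai Chi, meaning at least one class or any home practice.
- State that exercise-arm participants with no such exposure are not counted in the standard care column.

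The attendance lists and training diaries already planned under How well supply the exposure data, so nothing new has to be collected. The cost is a few sentences and one extra table. The randomised-arm table slightly dilutes exposure-related rates (9.0% instead of 10.0% in the illustration at 10% non-starters), which the exposure-based table covers.

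### The safety analysis promises adverse-event and serious-adverse-event rates, but the documentation rule keeps only events judged possibly related, so the data yield rates of related complications, probably tilted against the exercise arms

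*Protocol article*

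**What the plan says.** Two sections of the protocol article describe the safety data.

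- **Statistical analysis**, on what will be reported: "The rates of adverse events and serious adverse events will be calculated with a two-sided 95% CI". On the population: "Safety analyses will be performed for all participants for whom one of the interventions is started, and participants will be analysed according to the intervention" that they actually took up. Presentation by group is therefore implied, although the sentence on rates does not say so and names no test between arms.
- **Complications**, on what will be collected: "The complications that can arise from EYT, Tai Chi or other exercises will be collected monthly". The definition has causality built in: "A complication is any untoward medical occurrence such as any unfavourable and unintended sign, symptom, or disease that is possibly related to the study intervention". The question put to participants is wider: "participants are asked about any untoward medical occurrences or unplanned medical visits". The recording rule then narrows it: "In case of a possible relation to the intervention, these occurrences are documented, including severity and outcome". There is also an exclusion: "Not regarded as complications are conditions that were already present at the time of the informed consent", together with expected muscle ache. On falls, "injuries are reported as complications in case they occurred during training"; otherwise falls and fall injuries are trial outcomes. The FIMA questionnaire on service use is named as a further safety source.

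The Discussion allows that more complications may be recorded in the two exercise groups if those participants practise more, and offers open questioning and the FIMA as the answer.

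**The concern.** The analysis names one class of event and the collection rule keeps another. In ordinary trial usage an adverse event need not be caused by the treatment; a complication, as defined here, must be possibly caused by it. If both sections are followed as written, a count of related events will be published under an AE/SAE label.

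Two things are at stake. First, the level: a reader would take the figures as the burden of medical events in these patients, when they are a fraction of it. Second, the contrast: relatedness is judged by staff who know the allocation, and one arm has no trial classes to which an event could be attributed. The title of the trial claims an assessment of safety, and events that were never documented are hard to recover later.

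**Working it through.** The article states no AE or SAE rate, so there is no safety figure to reproduce. Its sample-size figure (155 per group) concerns fallers and does not bear on this point. The check is mainly a comparison of sections.

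**Step 1: follow one event through the plan.** Suppose a participant has an unplanned hospital stay for a cause that staff judge unrelated.

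1. The monthly open question elicits it. Table 1 schedules the safety item at every contact and does not restrict it to the exercise arms.
2. The recording rule applies after the answer. The event is judged unrelated and is not documented as a complication.
3. The analysis asks for the SAE rate. The event is not in the complication record.

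The stay may appear in the FIMA, but as service use reported by the participant, not as an event with severity and outcome.

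**Step 2: ask whether the filter acts equally in all arms.** The section on blinding says that neither participants nor outcome assessment can be reliably blinded, and that the control group is not offered regular training sessions. The same symptom is more easily linked to an intervention in someone attending classes than in someone given a brochure. Open questions do not help, because they come before the filter. The data monitoring committee is described as reviewing complications, which is the same filtered record.

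**Step 3: illustrate the size.** All event inputs here are assumptions.

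- Participants per arm: 550 / 3 ≈ 183.
- True risk of any adverse event, equal in all arms: q = 20% to 60%.
- Chance that an event is judged possibly related: r_E = 10–30% in an exercise arm, r_C = 0–10% in control.
- Recorded risk = q × r. Spurious difference = q × (r_E − r_C). Expected count = 183 × q × r.

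| q | r_E / r_C | Recorded, exercise | Recorded, control | Difference (points) | Expected counts |
|---|---|---|---|---|---|
| 20% | 10% / 0% | 2.0% | 0% | 2.0 | 3.7 / 0 |
| 20% | 10% / 2% | 2.0% | 0.4% | 1.6 | 3.7 / 0.7 |
| 20% | 20% / 5% | 4.0% | 1.0% | 3.0 | 7.3 / 1.8 |
| 20% | 30% / 10% | 6.0% | 2.0% | 4.0 | 11.0 / 3.7 |
| 60% | 10% / 0% | 6.0% | 0% | 6.0 | 11.0 / 0 |
| 60% | 10% / 2% | 6.0% | 1.2% | 4.8 | 11.0 / 2.2 |
| 60% | 20% / 5% | 12.0% | 3.0% | 9.0 | 22.0 / 5.5 |
| 60% | 30% / 10% | 18.0% | 6.0% | 12.0 | 32.9 / 11.0 |

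The level is wrong whatever the contrast: a true 20% is shown as 2–6% in the exercise arms, and a true 60% as 6–18%. The confidence interval does not repair this. If no event were recorded among 183 controls, the exact 95% interval would be 0 to 1 − 0.025^(1/183) = 2.0%. That describes the relatedness filter, not the incidence of adverse events.

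**The case against.** The strongest reply is that recording related events, backed by all-cause service use, is a defensible design for group exercise, and that the mismatch is one of terms. Much of this stands. The analysis section does not say *all* adverse events and promises no test between arms. The authors disclose the possible asymmetry themselves. No efficacy analysis is touched, and relabelling would remove the contradiction.

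Three stronger readings are tempting and are not supported.

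- *Control events will be near zero by construction.* The Complications section also covers exercise other than the two trial programmes. The standard-care brochure recommends training, and the blinding section says that controls can take up courses elsewhere. Control events can be recorded; only a lower rate is supported. A zero in an illustration is an assumption put in, not a result.
- *No randomised safety comparison is possible.* The FIMA is scheduled in every arm at baseline and months 3, 6 and 12. Moderate and serious injurious falls are outcomes in every arm whatever their cause. These are not an AE/SAE record, but they do give all-cause harm data.
- *Aggravation of existing disease is excluded.* The exclusion names conditions already present, while the definition admits any new unfavourable sign or symptom. The text is ambiguous on worsening. It matters because chronic disease is required for entry, but the text does not settle it either way.

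A last reply is that the full protocol may define AEs and SAEs. A definition alone would not restore events that the article's own rule leaves undocumented. If the full protocol does record them, the Complications section describes the collection wrongly and needs correcting.

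**Conclusion.** The two sections contradict each other. Under the stated documentation rule, AE and SAE rates cannot be obtained from the complication record; rates of possibly related complications can. Those rates understate the event burden in every arm and are likely to be lower in control because of how relatedness is judged.

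The contradiction itself rests on the text alone. The direction of the bias rests on unblinded judgement and the absence of classes in the control arm, and the Discussion partly acknowledges it. The size, about 1.6 to 12 percentage points with equal true risks, rests wholly on assumed event and attribution rates and shows only that the effect need not be trivial. This should be fixed, but it does not threaten the primary or other efficacy analyses.

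**What to change.** **Preferred.** In all three arms, document every untoward occurrence already elicited at the monthly contacts, or at the least every serious one. Record seriousness and relatedness as separate variables. State in the Complications section that worsening of a pre-existing condition after the start of observation counts. Report all events and serious events by arm, with related events listed separately.

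**Alternative, if collection cannot change.** Rename the analysis *rates of possibly related complications*, and state that these will not be interpreted as a comparison with standard care. Specify physician contacts and hospital stays from the FIMA, together with moderate and serious injurious falls, as the all-cause safety comparison between arms.

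**Cost.** The alternative is a change of wording. The preferred form needs a change to the case report form and extra documentation, but no new visit, because the question is already asked. Full recording is not negligible: 550 participants × 12 contacts gives up to 6,600 contacts at which events might need entry. Restricting full recording to serious events would cut this considerably.
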